**Methods and analysis:**

Twenty-five UK adults (aged 18 or over) with mild to moderate anxiety and/or depression and low adherence to an MDP were recruited to a cross-over randomised controlled trial. Each participant undergoes a 5 day MDP and a 5 day WD in a randomised order with all meals provided. The co-primary outcomes are mood and anxiety, with secondary outcomes including cognitive function, brain perfusion (as assessed by MRI), sleep quality, blood pressure, plasma glucose, insulin, lipids, C-reactive protein, cortisol, brain-derived neurotrophic factor, gut microbiota speciation and microbial metabolites including short chain fatty acids. A linear mixed model and/or paired analysis will be used to compare the effects of treatments over time.

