Participants are asked to visit the intervention centre on day 1 (figure 2), from 08:00 until approximately 15:30. Before their arrival, they are required to collect a urine and faecal sample at home using sample collection kit provided at least 2 days prior to their day 1 visits. The kit includes a stool sample catcher, two plastic tubes with scoop, a biohazard bag, a sealable bag, a urine sample collection pot with a sealable bag, a pair of disposable gloves, an insulated cool bag, two freezer blocks with two sterile outer bags and instructions. They are asked to collect the faecal sample within 24 hours prior to their clinical visit, and the urine sample as the first pass on the morning of their visit (day 1). Participants arrive at the intervention centre in a fasted state (fasted from 20:00 the night before). On arrival, anthropometric (weight and height) and blood pressure (BP) measurements are taken. A nurse collects the baseline blood sample. Participants are then provided with a honey and oat cereal bar. After 15 min rest, participants undergo the mood, anxiety, cognition and sleep testing via the study website; 90 min after completing these tests, participants are served either an MDP or a WD test meal (at 11:30) depending on the arm they are randomised to. Following the meal, participants’ BP is measured at 12:45 and start postprandial mood and cognitive testing at 13:00. At 14:00, they undergo the brain MRI scan and provide a postprandial blood sample at 15:15. Afterwards, participants are provided with an afternoon snack before leaving the unit and consume their day 1 dinner at home. On day 2 morning, participants complete online mood and anxiety testing at home after having a honey and oat cereal bar. On days 2–5, participants complete a sleep diary. An actigraphy is worn throughout the intervention period. On completion of the 5 day intervention, participants return to the intervention centre on the morning of day 6 (08:00–10:00) to repeat the morning assessments, as carried out on day 1 (figure 2).

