### Statistical methods: data collection, management and analysis

#### Sample size calculation

The sample size calculation was based on data from a previous cross-over trial of the effect of MDP adherence in a young healthy adult group.^67^ Assuming an error rate of 0.05 and 90% power, we would require 15 and 20 participants to complete each arm for the primary outcome, which is the contentment, a mood domain from the Bond-Lader scale (9.6 unit expected difference, SD 10.3). To account for up to 20% dropout between random allocation to treatment sequence and study completion, we recruited 25 individuals.

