#### Analysis

The main aim of the trial is to test if mood and anxiety can be improved over 5 days of intervention. The primary outcome analysis will use two-way repeated measures analysis with paired analysis taking mean change-scores.

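### The primary analysis subtracts each arm's baseline as a change-score; adjusting for it would be unbiased too and usually more precise, at almost no cost

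*Protocol article*

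**What the plan says.** The design is a two-period cross-over: "Each participant undergoes a 5 day MDP and a 5 day WD in a randomised order with all meals provided". Mood and anxiety are measured at a fresh baseline on day 1 of each arm ("After 15 min rest, participants undergo the mood, anxiety, cognition and sleep testing via the study website"). Table 4 lists them again after the test meal, at 24 hours and on day 6. The primary outcomes are Bond-Lader contentment and POMS anxiety.

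For the primary outcome, the Analysis section prescribes a two-way repeated-measures approach with "paired analysis taking mean change-scores". The abstract is looser and mentions a linear mixed model, a paired analysis or both. Neither place names baseline as a covariate.

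The sample size section gives inputs for contentment only: "Assuming an error rate of 0.05 and 90% power" and "9.6 unit expected difference, SD 10.3". From these, "we would require 15 and 20 participants to complete each arm for the primary outcome". It does not say whether 10.3 is the SD of change-score differences, of post-intervention differences, or of something else.

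**The concern.** Change-scores are often chosen to remove differences between people. Here the pairing has done that already, because each participant's Mediterranean-diet value is compared with the same participant's Western-diet value. A baseline in each arm can then explain only how the person happened to feel at the start of that particular period. If that state carries over only partly to day 6, subtracting it in full brings in the noise of two further measurements. Regression lets the data choose the coefficient.

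At stake is the width of the interval for the two primary outcomes in a trial planned around 20 completers and, under some assumptions, whether the planned 90% power is reached.

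**Working it through.** **The plan's own figure.** A two-sided paired t-test at 0.05 with standardised difference 9.6/10.3 = 0.932 has power 89.6% at n = 14 and 91.8% at n = 15. The stated 15 is therefore reproduced (the article does not state sidedness; two-sided is assumed). The 20 has no inputs of its own and cannot be checked. The recruitment figure follows from it: 20/(1 − 0.2) = 25, in line with "To account for up to 20% dropout between random allocation to treatment sequence and study completion, we recruited 25 individuals".

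**Variance of the diet contrast.** For one participant let B be the baseline difference (Mediterranean minus Western) and Y the day-6 difference. Assume both have variance σ² and correlation r. Per participant:

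- change-score, Y − B: 2σ²(1 − r)
- day-6 value alone, Y: σ²
- Y adjusted for B: σ²(1 − r²)

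In large samples the ratio of change-score to adjusted variance is 2(1 − r)/(1 − r²) = 2/(1 + r). Change-scores are also less precise than ignoring baseline altogether when 2(1 − r) > 1, that is, when r < 0.5.

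Estimating the slope multiplies the adjusted variance by about 1 + 1/(n − 3), which is 18/17 at n = 20. The ratio becomes 2/(1 + r) × 17/18:

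| r | large sample | n = 20 | simulated, n = 20 |
|---|---|---|---|
| 0 | 2.00 | 1.89 | 1.89 |
| 0.2 | 1.67 | 1.57 | 1.56 |
| 0.3 | 1.54 | 1.45 | 1.45 |
| 0.5 | 1.33 | 1.26 | 1.26 |
| 0.7 | 1.18 | 1.11 | 1.11 |
| 0.9 | 1.05 | 0.99 | 1.00 |

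The ratio equals 1 when 1 + r = 34/18, so the gain ends at r ≈ 0.89. The cost of a period term is not included in these figures.

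**Power for contentment with 20 completers** (difference 9.6, two-sided 0.05, noncentral t).

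*Reading A: 10.3 is the SD of change-score differences.* Change-score power is 97.7%, whatever r is.

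*Reading B: 10.3 is the SD of day-6 differences.* The change-score SD is then 10.3 × √(2(1 − r)):

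| r | change-score SD | completers for 90% | change-score power, n = 20 | adjusted power, n = 20 |
|---|---|---|---|---|
| 0 | 14.57 | 27 | 79.8% | 96.9% |
| 0.2 | 13.03 | 22 | 87.8% | 97.4% |
| 0.3 | 12.19 | 19 | 91.6% | 98.0% |
| 0.5 | 10.30 | 15 | 97.7% | 99.3% |

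Under B, change-score power is 89.7% at r = 0.25 and 90.1% at r = 0.26, so the crossing point is about 0.26.

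**Does the repeated-measures wording already adjust?** No. If baseline is one level of the time factor, the diet-by-time contrast of day 6 against baseline is the change-score contrast. A mixed model adjusts only if baseline enters as a covariate, and the article does not say that it does.

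**The case against.** The best defence is that the planned analysis is valid. Diet order is randomised, so change-scores are unbiased and keep the type I error rate. This stands: the issue is efficiency only.

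The size of the loss is also unknown. The article does not give r. Baseline and day 6 lie within one short period, while the two day 1 visits are 28 days apart, so mood shared within a period could make r moderate or high. This stands too, and is why a range is shown. It also means that the claim of adjustment winning at every r below 1 is a large-sample statement that fails at this trial's size once r nears 0.9.

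A reader might infer that this choice alone decides whether the planned power holds. The article does not support that. It takes both Reading B and r below about 0.26; under Reading A the plan has power to spare for contentment. A reader might also infer that intervals for cognition and blood markers are widened in the same way. The change-score sentence covers only the primary outcome analysis, and the article does not say how secondary outcomes are handled.

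Finally, a condensed article may leave covariates to a fuller plan, and the abstract's mixed model leaves room for one. This stands in part. But the Analysis section does not merely stay silent: it names change-scores as the primary estimator.

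**Conclusion.** The point holds as a near-free gain in precision, not as an error of validity. With 20 completers, adjustment would cut the variance by about 47% at r = 0 (1 − 1/1.89), 31% at r = 0.3, 21% at r = 0.5, 10% at r = 0.7, and by nothing near 0.9. These figures assume equal variances of the baseline and day-6 differences and an r that must be supplied from outside the article.

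A shortfall below 90% power for contentment is possible but conditional, as set out above. For POMS anxiety no effect size or SD is given, so it cannot be shown that there is power to spare.

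**What to change.** For contentment and POMS anxiety, regress the within-person Mediterranean-minus-Western day-6 difference on the corresponding baseline difference, with a period term. Equivalently, fit a mixed model to the day-6 values with diet, period, the arm-specific baseline and the participant's mean baseline. Report change-scores descriptively or as a sensitivity analysis. State which SD 10.3 is. The same adjustment may be used for secondary outcomes that have a baseline.

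The cost is one or two degrees of freedom, with no gain if r is near 0.9. No new data are needed, because mood and anxiety baselines are collected in both arms. The change does carry a procedural cost: the article puts data collection at June to December 2023 and says participants know their diet. A switch of primary estimator must therefore be recorded as a dated, justified amendment before outcome data are analysed, or it could look data-driven.

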### CBF data analysis steps

Data preprocessing: raw data will be converted into the Brain Imaging Data Structure format for standardised data organisation.Structural processing: individual subject-level processing includes structural image processing and segmentation and normalisation to enhance the quality of anatomical data.Single-subject ASL processing: specific processing steps tailored for ASL data will be applied at the individual subject level, including motion correction, registration, partial volume correction and quantification of perfusion.

Group-level analysis: group-level processing through template creation producing a group-average image and subsequent atlas-based ROI statistical analyses.^68^

### Machine learning analysis

Machine learning holds considerable potential for identifying biomarkers and enhancing clinical decision-making in varied contexts and is effective in discerning clinical interventions. Our study will use the Random Forest algorithm to enhance the interpretability of the heterogeneous data. This is a supervised machine learning approach recognised for its adeptness to handle missing values, alleviate data noise and mitigate the risk of overfitting making it a robust choice for our analytical framework.^69^

### Monitoring: incidental findings and adverse events

Measurements that are deemed to be outside the normal clinical range will be reported to GPs as incidental findings. Potential incidental findings may be noted from PHQ-9 and/or GAD-7 questionnaires, blood sample analysis or the MRI scans. Due to the nature of the intervention, that is, commercially available food products, no adverse events are expected. If participants feel in anyway adversely affected by any foods or the principal investigator feels an AE necessitates cessation, the participant will be advised not to continue, and the appropriate measures will be taken. All AE’s will be recorded and handled in accordance with Good Clinical Practice guidelines.

### Patient and public involvement

None.

## Discussion

The MediMood study is an efficacy trial which will provide evidence and mechanistic insights into the acute and short-term effects of an MDP on mental health and cognitive performance in UK adults.

MediMood is the first RCT examining the acute (postprandial up to 5 days) effects of an MDP on mood and anxiety as the primary endpoint. Its strengths are as follows: (1) its controlled intervention design informed by a systematic review,^25^ with standardised meals supported by full food provision and detailed preparation instructions, rather than dietary advice only, (2) its cross-over design,^70^ (3) assessment of several biological mechanisms which are hypothesised to mediate the effects of diet on mental and cognitive health, (4) combination of both objective and subjective assessment/measurement methods, (5) its focus on at-risk individuals for future major psychological and neurological disorders, (6) involvement of adults with no upper age limit as people suffer from mental disorders at every life stage and (7) considers the effects of the menstrual cycle on the study outcomes.

The main limitation of the study is that, to reduce the participant burden, we do not measure mood, anxiety and cognition every day. Second, our MRI scan is in a different location, which causes a delay in the postprandial blood collection. Given the nature of the diets, it is not possible to conduct a double-blinded intervention as participants know which diets they are following which may lead to an ‘expectation bias’.^29^ All clinical data, including MRI and biological samples will be anonymously analysed. Cross-over design requires participants to undergo two interventions which may cause attrition.^70^ However, as our intervention duration is only 5 days, we think it is a low risk for the MediMood study.

Day-to-day low mood, anxiety and poor cognitive performance can adversely affect quality of life for not only those with pre-existing mental and/or cognitive health complaints but also healthy individuals. Therefore, there is a need to identify safe and accessible approaches impacting short-term brain health, which is the focus of the MediMood intervention, which also has a strong mechanistic component. The results will help inform future management strategies and policies for individuals with mental health complaints and in the early stages of age-related cognitive decline.

## Ethics and dissemination

### Research ethics approval

The study has been approved by the London Queen Square, NHS Research Ethics Committee and Health Research Authority (22/LO/0796). Informed consent is provided by all participants in the presence of certified research personnel.

### Dissemination policy

The findings of the study will be disseminated through peer-reviewed publications, conference presentations, public outreach events, local and national news and academic blogs such as www.conversations.com for public members.

### Data deposition

Anonymised data may be made available on request for additional analysis, by contacting [name] (senior author).
